#### Canadian occupational performance measure satisfaction score.

COPM-S data will be summarized and analyzed in the same way as COPM-P. The best possible score for COPM-S is 10 points and the MCID for COPM-S is 2 points [27–29]. COPM-S analyses will be performed for the same study populations as defined for COPM-P.

#### Leg pain

Any participant who has no pain (pain score of 0) at baseline will be excluded from the mITT analysis since the condition of interest is absent. A change in pain score of 2 (measured on an 11-point numerical rating scale) is recognized as meaningful [37–39]; participants will, therefore, be classified as responders if their pain score improves by at least 2 points from baseline. The proportion of responders at Weeks 8 and 12 will be summarized by treatment group. The hierarchical test procedure will be used to evaluate the effectiveness of Revitive Medic^©^ Program 1 and Revitive^®^ Program 2. Responder analysis will be performed for the ITT, mITT, PP, and also the subset of participants with a baseline pain score of ≥ 2 (since participants with a baseline score of < 2 cannot meet the criteria for a clinically meaningful change).

#### Symptom score

Symptoms will be assessed at weeks 0, 8, and 12. A total symptom score will be calculated as: (the number of symptom days multiplied by the average intensity, summed across all 4 symptom domains) divided by 7. Total score can range from 0 (best outcome) to 40 (worst outcome). A score of 0 indicates that the symptom was not present but will be included in the calculation of total symptom score, since this provides valuable data on symptom totality. Any participant with a total score of zero at baseline will be excluded from the mITT analysis as the condition of interest is absent.

A domain score for each item will be calculated as: (the number of days multiplied by the average intensity) divided by 7. Each domain score can range from 0 (best outcome) to 10 (worst outcome). For calculation of individual domain scores, only symptoms present at baseline will contribute to the baseline and post-baseline symptom scores for the mITT analysis. Change to Weeks 8 and 12 will then indicate the evolution of symptoms that were present at baseline.

#### Deep leg blood flow

Blood volume and blood intensity will be measured using Doppler ultrasound before and during NMES. If week 0 data are deemed erroneous due to noise in Doppler images, the assessment can be repeated at week 8; the data considered of the best quality with minimal noise will be recorded. Since blood flow is only measured under a single waveform, Revitive Medic^©^ Program 1 and Revitive^®^ Program 2 are not distinguishable; for this endpoint, data for Revitive Medic^©^ Program 1 and Revitive^®^ Program 2 groups will be combined and summarized as a single group.

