### Intervention description {11a}

#### Revitive Medic© Program 1 and Revitive^®^ Program 2

Revitive, is an approved, commercially available, Class IIa NMES medical device produced by Actegy Limited that stimulates the sensory and motor nerves of the feet and lower legs; the device is CE marked and indicated to manage leg pain and discomfort and/or poor circulation due to inactivity, osteoarthritis, diabetes, peripheral arterial disease, and chronic venous insufficiency. Revitive Medic^©^ Program 1 uses device 3156ADi and a modified device (5520AR) is used for Revitive^®^ Program 2. The difference between these two devices is in the waveform design and the number and order of waveforms. Revitive Medic^©^ Program 1 uses a program of 15 waveforms that runs twice over 30 min; Revitive^®^ Program 2 comprises 6 waveforms delivered in a package of 10 that is run 3 times over 30 min. The electrical stimulation intensity is variable and is controlled and set by the user from 1 to 99 units.

Both devices deliver intermittent, low-frequency impulses through surface electrodes on the footpad to produce (strong) skeletal muscle contraction because of intramuscular nerve branch activation. The devices have an “IsoRocker,” which allows it to gently rock back and forth, creating involuntary ankle movement to replicate heel-toe raises. Both devices are pre-programmed to deliver a series of stimulation patterns that last approximately 60 s each; each pattern is made up of a sequence of stimulation pulses delivered in cycles at frequencies of 20 to 44 Hz and durations of 450–970 μs. Therapeutic levels are dependent on reaching an intensity sufficient to induce motor neurostimulation that causes calf muscle contraction but remains comfortable for the user. The optimal intensity level to induce muscle contraction varies from person to person and may depend on factors including plantar surface skin hydration and comfort.

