### Outcomes {12}

The primary endpoint for the study comprises a comparison of change in Canadian Occupational Performance Measure Performance (COPM-P) score from baseline to Week 8 for Revitive Medic^©^ Program 1 versus Revitive sham. COPM-P score is a self-evaluation measure of each participant’s current physical/ occupational performance status.

Secondary endpoints comprise:Change in COPM-P from baseline to week 12, comparing Revitive Medic^©^ Program 1 versus Revitive sham.Change in COPM-P from baseline to weeks 8 and 12 comparing Revitive^®^ Program 2 and Revitive sham.Change in Canadian Occupational Performance Measure Satisfaction (COPM-S) score from baseline to week 8, comparing Revitive Medic^©^ Program 1 versus Revitive sham and Revitive^®^ Program 2 versus Revitive sham. COPM-S score is a self-evaluation measure of each participant’s current satisfaction with their relevant physical/occupational performance.Change in leg pain from baseline to weeks 8 and 12, comparing Revitive Medic^©^ Program 1 versus Revitive sham and Revitive^®^ Program 2 versus Revitive sham; participants will rate leg pain using an 11-point numerical rating scale.Change in blood flow volume and intensity from baseline during device use, comparing Revitive versus Revitive sham.Change in symptom score from baseline to weeks 8 and 12 in terms of overall symptom score and each item (heaviness, tiredness, aching, and cramps), comparing Revitive Medic^©^ Program 1 versus Revitive sham and Revitive^®^ Program 2 versus Revitive sham.

Assessments conducted at the different study visits are presented in Table 1.

**Table 1 Tab1:** Study assessments in the NMES stimulation trial

	**Telephone assessment (≥ week − 1)**	**Baseline assessment** **(week 0)**	**Treatment period**	**Week 8**	**Week 12**
Eligibility	x	x			
Randomization	x				
Informed consent		x			
Demographics		x			
Medical history	x	x	x	x	x
Medications	x	x	x	x	x
Device issue and familiarization		x			
Device usage		x	x	x	
COPM		x		x	x
Symptom (heaviness, aching, tiredness, and cramps) scores		x		x	x
Leg pain		x		x	x
Doppler ultrasound		x		x^a^	
Adverse events		x	x	x	x

^a^For participants with poor quality Doppler data at week 0

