#### Deep leg blood flow volume and flow intensity

Deep leg blood volume will be assessed using Doppler ultrasound before and during the use of the Revitive device [36]; the IsoRocker on the Revitive device will be disabled during Doppler ultrasound, to minimize movement during assessment. Blood flow will be measured at the medial aspect of the ankle between the medial malleolus and the Achilles tendon, using the appropriate arterial ultrasound probe and pre-set volume flow algorithms on a duplex ultrasound machine. Two sets of recordings will be taken, pre-stimulation and 30 s into Waveform 5. Five seconds worth of data will be recorded at each time. The recording will then be broken down into individual frames, saved onto the scanner, and analyzed mathematically by MATLAB [36]. MATLAB analysis of frames determines peak flow volume and the peak intensity of flow within those 5 s. If baseline visit data are of insufficient quality due to noise, Doppler ultrasound can be repeated at week 8.

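### Blood flow: the reason for pooling Programs 1 and 2 is unsupported and in tension with the device description, and the choice between week 0 and week 8 recordings carries a risk of bias

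*Protocol article*

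**What the plan says.** All references are to the protocol article.

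- **Outcomes {12}** lists as a secondary endpoint: "Change in blood flow volume and intensity from baseline during device use, comparing Revitive versus Revitive sham". No program is named. The COPM, pain and symptom endpoints do name Program 1 and Program 2.
- **Deep leg blood flow volume and flow intensity** fixes the measurement: "Two sets of recordings will be taken, pre-stimulation and 30 s into Waveform 5". Each recording lasts five seconds. Frames are saved, and peak flow volume and intensity are computed from them in MATLAB.
- **Deep leg blood flow** (statistical methods) reasons that the programs cannot be told apart, "Since blood flow is only measured under a single waveform", and that their data for the two "groups will be combined and summarized as a single group". If week 0 images are judged erroneous because of noise, the scan can be repeated at week 8, and "the data considered of the best quality with minimal noise will be recorded".
- **Intervention description {11a}** covers the active devices, 3156ADi (Program 1) and 5520AR (Program 2): "The difference between these two devices is in the waveform design and the number and order of waveforms". Program 1 "uses a program of 15 waveforms that runs twice over 30 min"; Program 2 "comprises 6 waveforms delivered in a package of 10 that is run 3 times over 30 min".
- **Who will be blinded {17a}** and **Procedure for unblinding {17b}** say that the assessor would know active from sham while measuring flow, and that only the participant is unaware of allocation.

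**The concern.** Measuring under one waveform makes two programs indistinguishable only if that waveform is the same on both devices. The article never says so, and its description of how the devices differ gives reason to doubt it. If Waveform 5 differs between devices, the pooled contrast averages two stimuli and cannot show whether Program 1, the subject of the primary objective, raises flow.

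The second issue is independent of the first. For some participants the value analysed may come from week 8 instead of week 0. The decision rests on judged image quality. The article gives no criterion for that judgement and no masking of whoever makes it. A week 8 scan also differs in kind: it follows eight weeks of use, during which participants were told to raise the intensity as needed to keep it strong but comfortable.

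**Working it through.** **1. The texts side by side**

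| Question | What the article gives |
|---|---|
| Where is flow measured? | 30 s into Waveform 5 |
| How do the active devices differ? | Waveform design, number and order |
| Program 1 | 15 waveforms, run twice in 30 min |
| Program 2 | 6 waveforms in a package of 10, run three times in 30 min |
| Is Waveform 5 common to both? | Not stated |

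If the number is a position in the sequence, a difference in order or design could put different stimuli there. If it is a label for a shared waveform, the pooling reason works. The article does not say which.

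**2. Cost of separate contrasts**

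No flow effect, standard deviation or repeat rate is stated, so there is no flow figure to reproduce. The only input is the planned 39 per group (Sample size {14}), assuming complete flow data. In units of the common SD:

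- Pooled, 78 v 39: SE = √(1/78 + 1/39) = 0.1961
- One program, 39 v 39: SE = √(1/39 + 1/39) = 0.2265
- Ratio = 0.2265 / 0.1961 = 1.155, about 15% larger.

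**3. What pooling does under assumed effects**

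With equal arms the pooled effect is (d1 + d2)/2. Power is for a two-sided 5% test by the normal approximation. The effects, in SD units, are assumptions for illustration.

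| Program 1, Program 2 | Pooled effect | Power, pooled | Power, Program 1 alone |
|---|---|---|---|
| 0.6, 0.6 | 0.60 | 86.4% | 75.5% |
| 0.6, 0.3 | 0.45 | 63.1% | 75.5% |
| 0.6, 0 | 0.30 | 33.4% | 75.5% |

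Pooling gains power when the programs act alike. In the two unequal cases it loses power and hides the difference.

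**4. Choice of recording**

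The size of any bias cannot be derived. An outer case, which is *not* the rule in the article, is that a fraction f of active participants have two recordings with correlation ρ, the larger response is always kept, and sham is untouched. The upward shift is then f·√((1 − ρ)/π) SD.

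- f = 0.1, ρ = 0.7: 0.1 × √(0.3/π) = 0.031 SD; two-sided 5% error becomes 5.3%.
- f = 0.5, ρ = 0.3: 0.5 × √(0.7/π) = 0.236 SD; error becomes 22.5%.

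This shows only that the effect of a choice depends heavily on how many recordings are replaced and on what basis. Neither is known.

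**The case against.** **On pooling.** The device description compares whole programs; the pooling sentence concerns one waveform. Two programs can differ overall and still share one, and the pooling sentence reads naturally as saying that they do. Pooling also matches the endpoint in Outcomes {12}, and detailed waveform specifications may sit in the full protocol. This stands in part. A reader might infer that the two sections flatly contradict each other, or that pooling departs from the endpoint; the article supports neither. What remains is that the pooling reason depends on a premise that is not stated and that the device description puts in doubt.

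**On the recordings.** Repeats are limited to noisy week 0 data (also in the footnote to Table 1), the stated basis is noise and not the flow result, and the flow values come from MATLAB. The article does not say who judges quality. The lack of assessor blinding is disclosed and explained. A week 8 repeat with its own pre-stimulation recording would carry its own reference. All this is fair. A reader might infer that an unblinded assessor makes the choice and that it inflates the active effect; the article does not establish either. The risk remains, because the rule rests on judgement, no masked reader is named where only participants are blinded, and a within-session reference does not make first use and use after eight weeks the same measurement.

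**On size.** An effect in one program and none in the other is an extreme case, and similar effects favour pooling. Both are true, which is why the order of the contrasts should depend on the answer about Waveform 5.

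**Conclusion.** The point holds as two limited findings. First, the stated reason for pooling is unsupported and in tension with the device description; it would be sound if Waveform 5 were the same stimulus on both active devices. Second, the rule for choosing between week 0 and week 8 recordings carries a risk of bias of unknown size and direction.

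The one firm figure is the price of separating the programs: standard errors about 15% larger than pooled, assuming 39 analysable participants per group. The power figures rest on assumed effects, and the selection figures on a rule that the article does not adopt; neither estimates what will happen in this trial. The change is worth making because it is cheap, but the endpoint is secondary and mechanistic. The COPM-P comparison and the sample size are untouched.

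**What to change.** 1. State whether Waveform 5 is identical on devices 3156ADi and 5520AR.
   - If it is, keep the pooled contrast first, in line with Outcomes {12}, and show Program 1 v sham and Program 2 v sham as supportive.
   - If it is not, report the two programs against sham first, with the pooled contrast supplementary.
   - Either way, one three-group ANCOVA with the pre-stimulation value as covariate yields all three contrasts.
2. Use the week 0 recording in the main analysis. Accept a week 8 replacement only when week 0 fails a noise criterion fixed in advance and applied to the stored frames with arm labels removed.
3. Add a sensitivity analysis without week 8 replacements, and report the number of replacements by arm.

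**Cost.** Analysis wording and a masked quality read of frames that the article says are saved; no new data. Separate contrasts have standard errors about 15% larger than the pooled one. The sensitivity analysis loses participants whose week 0 scan failed. Removing labels may not mask fully if the signal during stimulation reveals the arm, so the criterion should be as objective as possible.

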### Interim analyses {21b}

To inform on response rates and provide baseline data for sample size calculation, a pilot study was conducted with the first 10 participants from each of the three groups (30 participants in total). Based on the pilot study, the responder rate was calculated for the Revitive sham, and an absolute risk difference was defined for determining the responder rate for Revitive Medic^©^ Program 1 and Revitive^®^ Program 2 needed to show treatment benefit. The difference in responder rates was then used to calculate the total sample size for the study. Data from the 30 participants from the pilot study will be included in the final analysis, as they followed the same protocol as subsequent participants. No hypothesis testing for stopping for futility or efficacy was conducted at the end of the pilot, and so the potential for inflation of Type I or Type II errors is considered negligible.

### Methods for additional analyses (e.g., subgroup analyses) {20b}

N/A—no additional analyses are planned.

### Methods in analysis to handle protocol non-adherence and any statistical methods to handle missing data {20c}

Data from this trial will be summarized and analyzed for the ITT, mITT, and PP populations; analysis of the mITT and PP populations will be considered secondary.The ITT population will include all enrolled and eligible participants who were randomized and used their assigned device at least once. The ITT population will be used to summarize demographic, device compliance, and all efficacy parameters.The mITT will include all enrolled and eligible participants who were randomized and used their assigned device at least once, and for whom the condition being assessed was present at baseline; a separate mITT population will be defined for COPM, symptom score, and leg pain, as these depend on the baseline score for each parameter. In cases where ITT and mITT populations are identical, only the ITT analysis will be presented.The PP population will include participants from the ITT population who were compliant with using their assigned device, defined as missing no more than 28 treatment sessions (minimum 75% compliance). Participants unable to confirm how many treatment sessions they missed will be excluded from the PP population. The PP population will be used to summarize COPM, symptom score, leg pain, and blood volume and intensity data.

Participants who discontinue the study will have data collected up to the point of discontinuation. For participants not assessed at week 8 or 12, the value will be left as missing for calculation and presentation of summary statistics. Participants who do not return their study device at the week 8 visit will be considered as having discontinued the study at this time; this ensures that the potential for continued use of the device after week 8 does not compromise study findings.

For statistical analysis, multiple imputation will be used to handle missing data. It will be assumed that data are missing at random. If the pattern of missing data is non-monotone, then partial imputation will initially be carried out (just enough to get the monotone missing data pattern) using the Markov Chain Monte Carlo method. Once the data exhibit a monotone missing data pattern, the monotone regression method will be used to impute the remaining missing data. The regression model will include terms for treatment and the observed values at visits prior to the missing value. For each endpoint, 20 imputed datasets will be created and analyzed, and the results will be pooled using the MIANALYZE procedure. Sensitivity analysis will be performed whereby missing data will be replaced by the value recorded at baseline (baseline observation carried forward).

For COPM-P responder analyses, participants who do not have an assessment for a visit will be categorized as responders or non-responders according to the value obtained via the multiple imputation; for sensitivity analysis, they will be classified a non-responder (non-responder imputation) at that visit.

### Plans to give access to the full protocol, participant-level data and statistical code {31c}

Study staff involved in the collection and analysis of data will have access to the trial data set. Access to the final cleaned dataset will be provided to the trial statistician for the purpose of carrying out the planned analyses. Ongoing access to the data will only be available to the study team for the purpose of carrying out related analyses.

## Oversight and monitoring

### Composition of the coordinating center and trial steering committee {5d}

N/A—this study will be conducted by the study investigator, who is responsible for ensuring that the trial is conducted according to the Medical Research Council Guidelines for Good Clinical Practice in Clinical Trials.

### Composition of the data monitoring committee, its role and reporting structure {21a}

N/A—the Revitive NMES device is a commercially available, CE-marked, Class II device with extensive use in the community setting, without safety signals occurring. As a result, the use of a data monitoring committee was not considered necessary.

### Adverse event reporting and harms {22}

The occurrence of AEs will be recorded throughout the study. Participants will be asked about the occurrence of such events at study visits. Adverse events of special interest will be identified as events with a potential causal association to the use of the study device. Any SAEs will be investigated by an independent medical monitor and reported to the ethics committee. A safety board will be convened if deemed necessary, e.g., where a trend in incidents or events is noted.

The Revitive NMES device is a commercially available, CE-marked, Class II device with extensive use in the community setting. As such the risk of SAEs is expected to be rare. Standard risk assessment was conducted for both the investigational device and the clinical investigation process and identified that all risks associated with the study were adequately controlled.

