## Interventions

### Explanation for the choice of comparators {6b}

The comparator chosen for the study is “Revitive sham.” This will enable the study to demonstrate how much placebo effect, if any, is achieved with the use of a sham treatment. The comparison between the Revitive sham and the intervention(s) will demonstrate whether the real treatment effects achieved with the active devices are statistically and/or clinically significantly different (i.e., superior) to the placebo effect. To enable successful blinding of the participants, the appearance and all functionalities of the sham device are kept identical to the active devices; however, unlike in the active devices, the stimulation intensity in the Revitive sham is limited to a maximum of 2 (of 99) units. Limiting the intensity level to 2 ensures that a clinically meaningful NMES is not delivered to the tissues, and it is assumed that any potential clinical benefit that may be achieved from this sham application amounts to a placebo effect.

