Following the 8-week intervention period, participants will return their device to the research team and will be assessed for Week 8 outcome measures. Participants will then return for a repeat assessment of all outcome measures at Week 12, following a 4-week follow-up period without device use. This post-intervention follow-up period is included to assess the short-term maintenance of the treatment effect.

Safety assessment comprises a formal evaluation of all adverse events (AEs), adverse events of special interest (events with a potential causal association to the use of the study device), and serious adverse events (SAE).

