### Concealment mechanism {16b}

At the time of recruitment, the researcher will allocate participant numbers sequentially to all participants. Each participant number has a pre-allocated study group as per the concealed randomization table, which the researcher is unaware of at the time of recruitment thus avoiding selection bias. Participants will be blinded to their intervention allocation throughout the trial and informed that they have a one in three chance of being randomized to a particular treatment group. It will not be possible to differentiate active and sham devices, as the packaging and appearance of all devices are identical. The same detailed “Instructions for Use” are given to participants regardless of the device they receive. Description of the sensations that can be experienced while using the device will be the same for all participants (a range of sensations from light tingling and feelings of pins and needles to noticeable muscle twitch and contractions in the feet and legs).

Familiarization and ongoing support with the device will be managed by the investigator, who will provide feedback and cues to the participant that their sensations/feelings in response to using the device are as expected/normal.

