## Assignment of interventions: blinding

### Who will be blinded {17a}

This will be a single-blind study with trial participants blinded as to the assignment to their study intervention. Conducting a double-blind study is not feasible, as the therapeutic functioning of the NMES device is dependent on reaching an intensity that results in visible contraction of the calf muscle; as such, the study assessor would be aware of whether the participant used an active or sham device during blood flow measurement.

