## Data collection and management

### Plans for assessment and collection of outcomes {18a}

Outcome and baseline trial data will be collected using a case report form administered by the investigator at each study visit. Images and data from the Doppler ultrasound will be acquired electronically at the baseline visit.

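### Adverse events of special interest are defined by suspected device causality while only the participant is blinded, so their counts by arm are at risk of attribution bias of unknown net direction

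*Protocol article*

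**What the plan says.** All references are to the protocol article.

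- **Definition.** Outcomes {12} lists three elements of the safety evaluation: all adverse events, "adverse events of special interest (events with a potential causal association to the use of the study device"), and serious adverse events. Adverse event reporting and harms {22} repeats the middle definition: "Adverse events of special interest will be identified as events with a potential causal association to the use of the study device". Neither place gives a list of event types or names who makes the judgment.
- **Collection.** Section {22} also states "The occurrence of AEs will be recorded throughout the study" and "Participants will be asked about the occurrence of such events at study visits". Table 1 marks adverse events at baseline, during treatment, and at weeks 8 and 12. Section {18a} says who completes the form: "Outcome and baseline trial data will be collected using a case report form administered by the investigator at each study visit".
- **Knowledge of allocation.** Who will be blinded {17a} says "the study assessor would be aware of whether the participant used an active or sham device during blood flow measurement", and Procedure for unblinding {17b} confirms that the participant alone is blinded. Under Implementation {16c} the investigator generates the sequence and assigns participants. Sequence generation {16a} says the device model number distinguishes the three groups.
- **Belief about sham.** Explanation for the choice of comparators {6b} says the intensity cap of 2 out of 99 units "ensures that a clinically meaningful NMES is not delivered to the tissues".
- **Reassurance.** Concealment mechanism {16b} gives familiarization and continuing support to the investigator, "who will provide feedback and cues to the participant that their sensations/feelings in response to using the device are as expected/normal".
- **Independent checks.** Section {22} provides an independent medical monitor for serious events. Section {21a} says there is no data monitoring committee.

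**The concern.** The sham arm is the trial's only benchmark for harm caused by the device. A category that admits an event only if someone thinks the device may have caused it works as a benchmark only if that opinion is formed in the same way in every arm. Here it may not be. Anyone who knows the arm, and accepts that sham delivers no meaningful stimulation, has a reason to call a sham complaint unrelated and the same complaint on an active device possibly related.

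The population makes this harder. Eligibility requires leg aching or pain, heaviness, tiredness or cramps. Soreness or cramp from stimulation resembles the condition that brought the participant into the trial, so many causality calls will be ambiguous and open to influence from knowledge of the arm.

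A second route works at an earlier step. The investigator's cues that sensations are normal could lead participants to mention fewer of them. Active devices are set towards the upper limit of tolerance and sham is capped at 2 of 99, so such sensations are probably more frequent on active devices. The article does not say where an expected sensation ends and a reportable event begins.

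At stake is the tolerability comparison for a device sold for home use without a prescription.

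**Working it through.** The plan states no figure for adverse events, so there is none to reproduce. The check separates the steps by which an event reaches each table, then puts assumed values through them.

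**Model.** For each arm let *r* be the true proportion with a relevant complaint, *c* the probability that a complaint is recorded as an adverse event, and *a* the probability that a recorded event is judged device-related. Then:

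- all-event rate = *r* × *c*
- special-interest rate = *r* × *c* × *a*

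The sections quoted above bear on these terms as follows: {12} and {22} make *a* the entry rule; {17a}, {17b}, {16a}, {16c} and {6b} give reasons why *a* may differ by arm; the cues in {16b} could lower *c*.

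**Attribution alone.** Assume *r* = 0.20 in both arms and *c* = 1. No document gives these values. Group sizes from Sample size {14} are 39 + 39 = 78 active and 39 sham.

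| *a* active / sham | Special-interest rate, active | Special-interest rate, sham | Risk ratio | All-event risk ratio |
|---|---|---|---|---|
| 0.5 / 0.5 | 0.20 × 0.5 = 0.10 | 0.20 × 0.5 = 0.10 | 1.0 | 1.0 |
| 0.6 / 0.4 | 0.20 × 0.6 = 0.12 | 0.20 × 0.4 = 0.08 | 1.5 | 1.0 |
| 0.8 / 0.2 | 0.20 × 0.8 = 0.16 | 0.20 × 0.2 = 0.04 | 4.0 | 1.0 |

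With equal *r* and *c* the ratio is *a*(active)/*a*(sham), whatever *r* is; true rates of 0.10 and 0.30 give the same 1.5 and 4.0. In the second row the expected counts are 78 × 0.12 = 9.4 and 39 × 0.08 = 3.1.

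**Adding unequal recording.** Keep *r* = 0.20 and *a* = 0.6 / 0.4. Suppose reassurance halves recording on active devices and has no effect on sham, an extreme assumption because the cues go to all arms:

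- special interest: 0.20 × 0.5 × 0.6 = 0.06 active against 0.20 × 1 × 0.4 = 0.08 sham, ratio 0.75
- all events: 0.20 × 0.5 = 0.10 against 0.20, ratio 0.5

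If recording were halved in both arms, the special-interest ratio would return to 0.06 / 0.04 = 1.5 and the all-event ratio to 1.0.

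**Reading.**
1. Unequal attribution distorts the special-interest comparison and leaves the all-event comparison untouched.
2. Unequal recording would distort both.
3. The two routes oppose each other, so the net direction cannot be derived from the documents.

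**The case against.** The case against has real force, and it rules out several stronger readings.

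- **That the whole harms comparison is biased by construction.** A reader might infer this, but the article records adverse events throughout and lists all of them in the safety evaluation. A sham complaint not labelled special interest is still counted. Bias in the subset also needs attribution to differ by arm, which is a risk and not a certainty.
- **That the unblinded investigator is the causality judge.** This is a fair inference from {16c}, {18a} and {5d}, which put assignment, data collection and conduct with that role. No section states it, and the full protocol may name someone else.
- **That reassurance replaces adverse event recording.** Section {16b} says cues will be given about sensations. The sensations described just before are tingling, pins and needles, twitch and contraction, and muscle contraction is the intended action. Nothing says such complaints are left out of recording or that reassurance comes first. The common description of sensations and the common instructions also support participant blinding.
- **That a planned test is invalidated.** The article describes no between-arm test of special-interest events. It explains why the assessor cannot be blinded and acknowledges this as a limitation.

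What remains is the definition itself. It is stated twice, makes causality the entry rule, and has no blinded or independent check stated for non-serious events. Recording all events protects the total, not this category, which {12} lists as a separate element of the safety evaluation. The acknowledged limitation does not mention harms.

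**Conclusion.** The concern holds as a risk of bias confined mainly to one category. Counts of special-interest events by arm depend on a causality judgment that the article does not shield from knowledge of the allocation, so a difference between active and sham could not be read as a device effect, nor the absence of one as reassurance.

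The size cannot be established from the documents. Under assumed attribution probabilities from 0.5 / 0.5 to 0.8 / 0.2, and with no true difference, the apparent risk ratio runs from 1.0 to 4.0. Adding an assumed loss of active-arm reports can bring it below 1. These values show sensitivity; they are not estimates. The all-event comparison does not depend on attribution and is the sounder one, with the caveat that the questioning behind it is unblinded.

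The conclusion assumes that whoever judges causality knows, or can learn, the arm. If the full protocol assigns that task to someone blind to allocation, the attribution part falls away. The efficacy analyses are not affected. The point is worth correcting because the change is cheap.

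**What to change.** 1. In Outcomes {12} and Adverse event reporting and harms {22}, define special-interest events by a prespecified list of event types, applied to all recorded adverse events regardless of suspected cause or arm. The sponsor should choose the terms on clinical grounds; skin reactions at the footplates, new or worse leg pain, cramp, and sensations that persist after a session are examples of the kind of entry meant.
2. Tabulate causality separately, and do not use it as an entry criterion.
3. Name the rates of all adverse events by arm as the main harms comparison.
4. State in {16b} or {22} that telling a participant a sensation is expected does not exempt the complaint from being recorded as an adverse event. The cues themselves should stay uniform across arms, because restricting them could affect participant blinding.

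**Cost.** Wording in two or three sections and a term list, with more minor events tabulated in all arms. Items 1 to 3 work on events already recorded, so they can still be applied in full if the list is fixed without reference to the data by arm. Item 4 comes late: Trial status gives recruitment as completed on 30 June 2022 and study completion as estimated for 31 October 2022, so it can reach only participants still in follow-up. None of these changes removes the unblinded elicitation, which should be reported as a limitation of the harms data.
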